## Abstract

**Clinical trial registration:**

https://clinicaltrials.gov/study/NCT06197477, Identifier NCT06197477.

## Introduction

1

According to the 2025 OECD countries (Organization for Economic Co-operation and Development) report on education, primary school children spend on average 804 h per year in the classroom, which makes approximately 31% of their waking hours on school days (1). These classrooms are characterized by substantially higher occupancy densities compared to most other building types, sometimes reaching density levels up to four times greater than those observed in typical office environments (2). Despite school efforts to improve indoor air quality (IAQ), students are still frequently exposed to suboptimal conditions (3). Exposure to poor IAQ has been shown to significantly impact children’s health, comfort, and academic performance. Moreover, prolonged exposure to indoor air pollution can contribute to cardiovascular and respiratory diseases, adversely affect the central nervous system, and result in cognitive impairment and developmental delays (4–12). Children are particularly vulnerable due to their developing organs and physiological systems, higher breathing rates, and behaviors that increase their exposure (7). Ultimately, managing IAQ in educational facilities is crucial, as it directly affects their health, academic performance, and attendance (13).

Volatile organic compounds (VOCs), semi-volatile organic compounds (SVOCs), and ultrafine particles (UFPs) are the indoor air pollutants of major concern due to their potential impacts on children’s health and development (4, 9, 14–16). Current strategies to improve IAQ in schools, such as opening windows for ventilation, help dilute indoor pollutant concentrations with outdoor air. However, this approach only works in areas with clean outdoor air and is problematic for schools located near busy roads (4). In such cases, pollutants such as combustion by-products, ozone (O₃), and allergens, among many others, can enter the classroom (17). Additionally, natural ventilation is not a viable option in unfavorable weather conditions. In these situations, using an air purifier can be an effective mitigation strategy to improve classroom IAQ (18–21).

Current epidemiological evidence on the association between air purifier use and health outcomes remains limited and inconsistent, especially regarding the primary school setting (18). Although recent studies indicate that filtration-based systems can improve IAQ as well as respiratory health, cardiovascular parameters, and academic performance, substantial gaps in the evidence persist (5, 18, 22). These gaps arise from a shortage of air quality intervention studies in primary school settings, coupled with highly variable regional exposure levels. To overcome this, future research must establish a more globally diverse framework that incorporates real-time data across varying exposure levels, allowing for a comprehensive evaluation of the overall health effects in this vulnerable population.

The use of human biomonitoring to assess internal exposure and early biological effects of environmental chemicals also remains underutilized, particularly in vulnerable populations such as children, which is identified as one of the priority areas in the European Exposure Science Strategy (23, 24). Environmental monitoring measures only ambient concentrations, whereas biomonitoring accounts for individual variations in inhalation rates, physical activity, and metabolism. By quantifying the actual internal doses, biomonitoring directly links environmental exposure to physiological uptake, providing more precise exposure metrics to refine exposure-response relationships (25). Consequently, there is a clear need for integrated studies that combine environmental monitoring, biomonitoring, and cognitive assessments within real-world intervention frameworks across multiple European school settings.

The European Union-funded project, LEARN (deveLopment of novEl Assessments for indoor aiR quality moNitoring and impact on children’s health), aims to better understand IAQ in schools and investigate its impact on children’s cognitive performance and general health, and evaluate the efficacy of air purification. To achieve this, the study introduces an integrated, multi-country trial across Belgium, Denmark, and Greece. The study’s primary novelty lies in its paired framework, which links classroom air quality data, including concentrations and profiles of indoor and outdoor air pollutants and microclimate parameters, with advanced human biomonitoring to track internal pollutant exposure alongside children’s health outcomes. Furthermore, the intervention utilizes a novel air purification system engineered and customized by MANN+HUMMEL specifically for this study. By evaluating this innovative technology across distinct geographic regions, LEARN will directly link environmental exposure to physiological uptake, providing a robust framework to optimize children’s health and cognition in educational environments and to investigate the efficiency of air purification.

## Study design

2

Here, we describe the study protocol of a single-blinded (teachers/students blinded) crossover intervention study conducted as part of the LEARN project. The study aims to evaluate IAQ in schools, the level of exposure, and its effects on the health and well-being (cognition, blood pressure, quality of life) of school children aged 9 to 12 years old. Additionally, this study explores improved approaches for characterizing IAQ and evaluating intervention effectiveness. A crossover design was selected to allow each participant to serve as their own control, thereby reducing inter-individual variability and increasing statistical power in detecting short-term effects of IAQ interventions.

### Study setting and eligibility criteria

2.1

LEARN is a multicenter study with case study sites in three European countries: Belgium, Denmark, and Greece. The Belgian study population is recruited from the Flemish Region of Belgium, in the Flemish provinces of Limburg, Antwerp, and Flemish Brabant. For the Danish and Greek sites, recruitment focuses on primary schools in the municipality of Aarhus and in Thessaloniki, respectively.

According to geographical location (feasibility, deprivation, etc.), schools are contacted (mail, phone, video call) for participation. The principal completes a questionnaire providing a detailed description of the school’s infrastructure. Schools with an air filtration system and/or policies requiring windows to remain closed are excluded. Sufficient space should also be present in the classrooms to position the filtration devices optimally, with at least 30 cm of clearance around them, to ensure effective intervention. For reasons of generalizability and external validity, we intentionally avoid imposing additional restrictive exclusion criteria. This approach ensures that the study remains representative of the real-life school environments where such interventions would be implemented.

Any primary school located in the included regions of Belgium, Denmark, or Greece complying with these criteria can participate, provided that at least two classes from the same school from the 4th, 5th, and/or 6th grade agree to take part in the study. Once the classes are confirmed, an information session is organized with the principal, teachers, parents, and students. During this session, the study is explained to the students in an age-appropriate manner. Additionally, each child receives an envelope containing detailed information about the study and a consent form for their legal guardian(s) to sign. Insufficient knowledge of the Dutch, Danish, or Greek language by the child or the child’s guardian(s) leads to exclusion from the study, due to the availability of study materials limited to these languages.

### Sample size calculation

2.2

A linear mixed-effects model will be applied to evaluate the association between the IAQ, the intervention, and the measured clinical parameters and biological biomarkers. Random intercepts will be specified for school, class, and child, and site-specific estimates will be combined through meta-analysis. As no pilot data were available across all sites, a simulation-based power analysis was conducted in R. The simulations assumed a within-person residual standard deviation (SD) of 1, and intra-class correlations (ICCs) of 0.05 for school, 0.10 for class, and 0.50 for child. For each scenario, 1,000 datasets were generated. In each dataset, the group × time contrast at the final time point was estimated using a linear mixed model, and site-specific results were combined via random-effects meta-analysis. The proportion of simulations yielding a two-sided *p* < 0.05 was recorded. Results indicated that recruiting approximately 150 children per country would provide 90% power to detect a medium-sized standardized intervention effect (Cohen’s d = 0.5 SD). This medium effect was selected as a pragmatic benchmark and should not be interpreted as the minimum clinically important difference for each outcome. We acknowledge that smaller effects than d = 0.5 SD may still be clinically or public-health relevant, but our study may have limited power to detect such smaller effects, and null findings should therefore be interpreted with caution.

### Sampling timeline

2.3

The LEARN study consists of four phases and takes approximately 6 to 7 weeks to complete for each school (Figure 1).

Baseline Period (BaP): No intervention is implemented at baseline (1 week).The participating classes are randomly assigned to one of two sequences in the crossover design: either starting with the intervention phase (installation of air purification units with filters) followed by the control phase (sham-intervention with installation of air purification units without filters)(R1), or vice versa (R2). Randomization is performed at the class level using computer-generated random numbers. The study is single-blinded, hence participants and teachers are unaware of the assignment of the intervention phase.Intervention Period 1 (IP1): The assigned (sham-) intervention is implemented and administered over 2 weeks.Washout Period (WP): A washout period of 1 to 2 weeks follows IP1, ensuring that the acute environmental and physiological effects of the initial intervention are fully diminished to maintain a true crossover design (26–29). Furthermore, this timeframe accommodates the academic calendar and classroom scheduling constraints. Potential carry-over effects will be further evaluated and adjusted for in the statistical analysis.Intervention Period 2 (IP2): The intervention status switches between the two groups, and the second phase of the study is conducted.

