## Health outcomes

4

To investigate the health impact of IAQ and the planned intervention, cognitive performance and blood pressure (BP) are assessed as primary outcomes at multiple time points. Additionally, clinical examinations evaluate secondary outcomes, including psychological well-being, anthropometric measurements, and the skin microbiome. All measurements are performed in an examination room provided by the participating school. The examination room is appropriately lighted and ventilated. A CO₂ measuring device is placed to monitor air quality levels. CO₂ levels are regulated by opening windows and doors at appropriate times. Two testing days are scheduled at BaP. The subsequent testing days occur on the final day of IP1 and the final day of IP2 (Figure 7).

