
Children perform the cognitive tests at four time points (Figure 7). During the BaP, each child completes all cognitive tests twice on different days to account for potential learning curve effects (57). Afterward, the children repeat the tests during the intervention and sham-intervention phases on the testing days to evaluate the impact of IAQ. To control for any residual learning effects, the specific intervention period will be included as a covariate in the mixed-model analysis. Cognitive testing is standardly performed between 08:00 and 12:00 h to account for variations in concentration dependent on the time of day (58, 59). The supervisor documents possible distractions and lapses in concentration. Children are given a score based on their attentiveness during the cognitive testing (0 = no problem, 1 = distracted, 2 = influenced by someone, 3 = external distractions, 4 = did not understand the task, 5 = bored, 6 = other). A score is assigned for each of the cognitive tests. Reasoning for the score is also noted down.

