### Main strengths and weaknesses

6.2

The key strength of this study lies in its design. Comparing health outcomes, internal biomarkers, cognitive function, and well-being with IAQ before and after the application of a novel remediation strategy in a single-blinded crossover design allows for the precise determination of the effectiveness of the intervention. The crossover design also allows the same group of children to serve as their own controls, minimizing variability and providing a better understanding of the intervention’s health benefits. Due to the practical necessity of researchers installing the equipment, a single-blinded design was employed.

Another strength of this study is the carefully designed cognitive testing protocol. The potential for training effects was addressed by including two practice sessions during the BaP (57). Additionally, the use of standardized audio instructions ensures consistent delivery of test explanations across participants. Earlier studies often relied on oral explanations given by test administrators, which can introduce variability and potentially influence the results (65).

The same logic applies to the BP measurements. A baseline measurement is performed to allow children to become familiar with both the procedure and the researchers. During the BP assessments, five consecutive measurements are taken at each time point; the first two serve as internal acclimatization and will be excluded from the final analysis. This approach helps to minimize stress-related responses that can elevate BP readings during initial assessments (66). By addressing the acclimatization effect, the reliability of the blood pressure data is improved.

A third strength of this study is the modified standardized screening questionnaire with a scoring system. These questionnaires are given to and completed by the school staff responsible for each participating class. This enables easy identification of potential sources of indoor air pollutants in participating classrooms and ensures comparability between the two participating classrooms before the sampling campaign.

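### Adjusting for carry-over, as section 2.3 promises, would remove the second period from the treatment estimate and with it the own-control contrast that justified the crossover

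*Protocol article*

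**What the plan says.** Section 2.3 (Sampling timeline) sets out a two-sequence, two-period crossover: "The participating classes are randomly assigned to one of two sequences in the crossover design". Allocation is by class: "Randomization is performed at the class level using computer-generated random numbers". Between the periods, "A washout period of 1 to 2 weeks follows IP1", which the section presents as enough for acute effects to disappear. It then adds: "Potential carry-over effects will be further evaluated and adjusted for in the statistical analysis".

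Section 4 (Health outcomes) names cognition and blood pressure as primary. It schedules two baseline testing days, and then "The subsequent testing days occur on the final day of IP1 and the final day of IP2". Blood pressure has one baseline measurement (section 4.2). For cognition, "During the BaP, each child completes all cognitive tests twice on different days" (section 4.3). Neither is measured after washout and before the second period (IP2) starts.

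Section 2 gives the reason for the design: "A crossover design was selected to allow each participant to serve as their own control, thereby reducing inter-individual variability and increasing statistical power". Section 6.2 repeats it as a strength: "The crossover design also allows the same group of children to serve as their own controls". Section 5.3 describes the model as random intercepts for school, class and child plus covariates, and section 4.3 adds the intervention period as a covariate. Neither section mentions carry-over, so neither limits what section 2.3 promises.

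**The concern.** In a two-sequence, two-period crossover, the IP2 difference between sequences mixes the treatment effect with any carry-over from the first period (IP1). If carry-over is a free parameter, it absorbs that difference completely and IP2 carries no information on treatment. The promised adjustment would then replace the comparison the crossover was chosen for by a comparison between classes.

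The sentence can also be carried out in two stages: test for carry-over, and switch to the first-period analysis if the test is significant. The carry-over test and the first-period test share data, so the overall procedure does not hold its 5% level. What is at stake is the precision of the primary estimate under one reading and its error rate under the other.

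**Working it through.** **Inputs.** From section 2.2: residual SD 1; intra-class correlations 0.05 (school), 0.10 (class), 0.50 (child); about 150 children per country in three countries; effect 0.5, taken here in residual SDs; two-sided 5%; random-effects meta-analysis. Assumptions, because the article does not give them: 1:1 allocation (75 per sequence per country), 10 to 25 children per class, and both sequences present within each school, so that the school effect cancels.

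**The plan's own figure.** Section 2.2 powers the group-by-time contrast at the final time point. As a change from baseline, 75 against 75, its SE is √(2 × 2/75) = 0.231. Power is 0.58 in one country and 0.91 after random-effects pooling of three, which reproduces the stated 90%. The within-child contrast does not: its power is 0.99 in one country and 1.00 pooled.

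**Weights.** Let τ be the treatment effect and λ the carry-over, as differences between sequences. The IP1 difference estimates τ and the IP2 difference estimates λ − τ.
- Without λ, the weights on (IP1, IP2) are (0.5, −0.5).
- With λ free, they are (1, 0). This follows from the algebra and does not depend on class size.
- With one baseline and 15 children per class, they are (baseline −0.85, IP1 1, IP2 0).

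**Variances, 15 children per class.** The residual share is 1 − 0.65 = 0.35, so the class variance is 0.10/0.35 = 0.286 and the child variance 0.50/0.35 = 1.429. For a class mean, the stable part is b = 0.286 + 1.429/15 = 0.381 and the residual part is w = 1/15 = 0.0667. With five classes per sequence, SE = √(2 × variance/5).

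| Estimate | Variance per class | Ratio | SE per country |
|---|---|---|---|
| Within-child, no carry-over term | w/2 = 0.0333 | 1 | 0.115 |
| Carry-over term, one baseline | b + w − b²/(b + w) = 0.123 | 3.7 | 0.222 |
| Carry-over term, two baselines | b + w − b²/(b + w/2) = 0.097 | 2.9 | 0.197 |
| Carry-over term, no baseline | b + w = 0.448 | 13.4 | 0.423 |

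Over 10 to 25 children per class, the ratios are 3.6 to 3.8 (one baseline), 2.9 (two) and 10.6 to 19.1 (none).

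**Pooled power at 0.5** (random-effects pooling): 1.00 for the within-child contrast. With a carry-over term it is 0.92 to 0.93 (one baseline), 0.97 (two) or 0.33 to 0.54 (none).

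**A smaller effect, for illustration.** Take half the planned effect (0.25), fixed pooling, 15 per class, and power = Φ(0.25/(SE/√3) − 1.96).
- Within-child: Φ(0.25/0.0667 − 1.96) = 0.96.
- Carry-over term, one baseline: Φ(0.25/0.128 − 1.96) = 0.50.
- Carry-over term, two baselines: Φ(0.25/0.114 − 1.96) = 0.59.

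**Test-then-adjust.** Assume no treatment effect and no carry-over, with a pre-test at 10%. When the pre-test is not significant, the within-child test is used; it is independent of the pre-test, so it contributes 0.90 × 0.05 = 0.045. When the pre-test is significant, the first-period test falsely rejects in about 36% of cases with one baseline, contributing 0.10 × 0.36 = 0.036. The total is about 0.081. Simulation (500,000 draws) gives:

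| Pre-test level | One baseline | Two baselines | No baseline |
|---|---|---|---|
| 10% | 0.082 | 0.077 | 0.091–0.094 |
| 5% | 0.074 | 0.070 | 0.083–0.087 |

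**The case against.** The article names no pre-test, no switching rule and no free carry-over parameter. The model in section 5.3 contains none, and such detail commonly sits in an analysis plan that is not shown here. That is fair, and it makes the type I error figures conditional on a procedure the protocol does not state. It does not dispose of the point, because section 2.3 does not merely leave the method open: it commits to adjusting. The milder readings are not adjustments. A sequence term leaves the within-child estimate unchanged and removes no carry-over bias, and the period covariate deals with learning.

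A reader might infer that adjustment would wreck the trial's power. The documents do not support this. The stated 90% belongs to a less precise contrast than the within-child one, and the adjusted estimate still reaches it at 0.5 SD if the baseline is modelled. Power collapses only if the baseline is left out, and nothing in the article says it will be.

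Nor is all own-control information lost. Each child's baseline still enters the adjusted estimate; what goes is the comparison of the same child under intervention and under sham.

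Evaluating carry-over is also reasonable in itself. Washout length varies, and urine has a post-washout sample on the first Monday of IP2 (section 3.2.2). Urine is limited to Belgium and Denmark, however, and is not a primary outcome. The objection here is to the promise to adjust.

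**Conclusion.** The concern holds as a should-fix, not as a fatal flaw. Taken at its word, section 2.3 gives IP2 zero weight for the primary outcomes and removes the contrast on which sections 2 and 6.2 rest the design. The zero weight is exact for any free carry-over term.

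The size is a variance about 3.6 to 3.8 times larger for blood pressure and about 2.9 times for cognition if both baseline sessions are modelled. These ratios depend on the planned intra-class correlations and on the assumed class sizes, allocation and cancelling of the school effect. The practical loss lies in precision and in power below 0.5 SD, where section 2.2 already concedes that relevant effects may be missed.

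A reader might also infer that the protocol prescribes a two-stage test. It does not. The 7 to 9% error rate applies only if the sentence is carried out that way, which its wording leaves possible.

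**What to change.** Replace the sentence in section 2.3. State that:
- the primary estimate is the period-adjusted within-child contrast of intervention with sham, resting on the washout;
- no carry-over term is fitted, and no carry-over test decides the analysis;
- the baseline-adjusted IP1 comparison is reported as a pre-specified sensitivity analysis;
- results in schools with a 1-week and a 2-week washout are compared as an exploratory analysis, noting that washout length is not randomised.

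The change costs one sentence and needs no new data. Its downside is that the primary estimate then rests openly on the assumption that the washout suffices. If carry-over did occur, the estimate would be biased, and the sensitivity analysis could show this only with limited precision.

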**Figure 1 fig1:**
[figure not shown]
Schematic diagram of the single-blinded crossover study design in the LEARN study.

Throughout the various study phases, data collection is divided into exposure assessment (detailed in Section 3) and health outcome measurements (detailed in Section 4). These activities evaluate children’s external and internal exposure to selected pollutants, alongside their cognitive function, clinical parameters, and skin microbiome.

